### Interventions

(1)Interventions: Neonates will be placed in a blue light treatment box (Ningbo David Medical Device Co., LTD, XHZ model) with the temperature set at 30°C and relative humidity at 55%. Phototherapy eye masks (Foshan Forman Medical Technology Co., Ltd., Yuesun Mechanical Equipment No. 20160015) and phototherapy diapers (Foshan Baojusheng Medical Equipment Co., Ltd., GB/T33280) will be used to cover the eyes and perineum. The treatment will involve LED blue light continuous irradiation with a wavelength of 425–475 nm. All neonates will undergo continuous phototherapy for 12 h, rest for 6–8 h, and then receive another 12 h of continuous phototherapy. The decision to continue with the next 12 h treatment session will depend on the changes in the neonate's jaundice condition.(2)Study drug and specifications: The patented probiotic combination (contains Bifidobacterium breve 10^9^, Lactobacillus rhamnosus 10^9^ and Bifidobacterium animalis 10^9^ per package) (invention patent, 202,010,414,426.7) will be added to the corresponding groups. The aforementioned drugs are freeze-dried powder, stored at room temperature, with a 30-month shelf life, and manufactured by China Taiwan Jinqiao Biological Co., Ltd. Probiotics intervention: the probiotics will be administered to jaundiced newborns requiring phototherapy. The experimental group will receive the corresponding daily probiotics during phototherapy. The probiotics will be mixed into the milk and consumed once a day, with a treatment course lasting for one month. Clinical study criteria will be controlled to determine the termination of the study.(3)Criteria for stopping the clinical study: (1) occurrence of serious adverse events occur that may be related to the use of probiotics; (2) if the planned interim analysis achieves the expected difference in efficacy and the intervention is observed to be significantly more effective in the trial group compared to the control group.(4)Adverse event observation
(1)Definition of adverse events: In this clinical trial, adverse events are defined as severe vomiting, diarrhea, disruption of normal eating habits, or significant necrotizing enterocolitis occurring during the use of probiotics. Additionally, an adverse event is defined as a severe increase in jaundice value that reaches the index for exchange transfusion.(2)Diagnostic criteria of adverse events: (1) Severe vomiting:vomit 5 or more times per day for 2 or more days; (2) Diarrhea 8 or more times per day for 2 or more days; (3) Necrotizing enterocolitis:Neonatal necrotizing enterocolitis is diagnosed according to the Clinical guidelines for the diagnosis and treatment of neonatal necrotizing enterocolitis (2020); (4) According to the Clinical Practice Guideline Revision: Management of Hyperbilirubinemia in the Newborn Infant 35 or More Weeks of Gestation, exchange transfusion criteria have been met.(3)Degree of adverse events: (1) Mild: Neonates can tolerate the event, which does not affect treatment, does not require special treatment, and has no impact on the neonates' health. (2) Moderate: Neonates find the event unbearable, affecting the treatment and having a direct impact on their health. (3) Severe: The event endangers the neonate's life, potentially causing death or disability, and requires immediate emergency treatment.(4)Possibility of adverse events: Although every bacterium in the probiotic combination used in this study is approved by the National Ministry of Health as safe and reliable, adverse events cannot be completely ruled out. However, the probability of adverse events is expected to be low(5)Treatment of adverse events, follow-up methods, and time: In case of adverse events, the incident will be promptly reported, and the clinical trial for the affected neonate will be terminated in a timely manner to prioritize their safety. The patient's stool and gastrointestinal symptoms will be monitored daily, and plain abdominal radiographs will be performed as needed. For patients with severe jaundice requiring exchange transfusion, exchange transfusion therapy will be immediately initiated, as well as monitoring jaundice dynamically and conducting brain MRI and brainstem auditory evoked potential assessments. Post-discharge follow-up will be conducted, selecting various follow-up methods based on the situation. If a neonate with jaundice experiences adverse events after taking probiotics or if such events are suspected to be related to the probiotic administration, strict records should be maintained, the adverse event form should be completed, and the main responsible personnel and the Clinical Research Center of the East Hospital of Shanghai Sixth People's Hospital will be informed within 24 h according to the established process. The ethics committee will decide whether to halt the trial immediately.(6)Risk prevention of adverse events: All adverse events occurring during treatment will be graded according to severity and documented in detail using a CRF (Case Report Form). The potential relationship between adverse events and probiotics will be analyzed. If severe adverse reactions occur, the trial should be stopped immediately. Serious adverse events must be reported in strict accordance with the relevant provisions of GCP (Good Clinical Practice). The group will not receive any drugs or additional probiotics in their milk.

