### Sample size

In previous clinical trials investigating the effects of probiotics on phototherapy, it was observed that the use of probiotics reduced the incidence of digestive tract side effects caused by phototherapy. Based on the results of a literature review, it was found that the general incidence of such side effects is approximately 47%, and our goal is to reduce this incidence to about 10% by adding the appropriate combination of probiotics. To achieve this goal, a margin of 0.05 was assumed, with a type I error of 0.05 and a power of 0.8. Using a difference test for two-sample ratios, a sample size of 20 cases per group was calculated, resulting in a total of 100 cases in both the experimental and control groups.

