### Randomization

(1)The randomized scheme of this experiment will be as follows: 100 cases are planned to be enrolled and divided into 5 groups: C0 (pure phototherapy group), T1 (treatment group 1), T2 (treatment group 2), T3 (treatment group 3) and T4 (treatment group 4), with 20 cases in each group.(2)The random system parameters will be set as follows:
•Random system: Taimei Medical eBalance random system•Random method: block random•Block length: 5•Number of blocks: 20•Random number: P001–P100.

The random operation steps would be as follows: The random-related parameters are determined according to the project's random scheme. The eBalance stochastic system is configured according to random parameters. The eBalance random system generated a random grouping table according to the configuration (calling SAS software). The eBalance random system exported the random grouping table.

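### An interim efficacy rule can stop all five arms on an undefined significant result in an unnamed arm, while the trial is sized as one fixed-sample test at 0.05

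*Protocol article*

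**What the plan says.** Interventions, item (3), lists two criteria for stopping the clinical study. The first concerns serious adverse events. The second is efficacy: "if the planned interim analysis achieves the expected difference in efficacy and the intervention is observed to be significantly more effective". The comparison meant is that of the trial group with control. Both parts must be met. The item states no timing, number of looks, significance level or boundary.

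Sample size describes a single comparison of two proportions. It takes a side-effect incidence of about 47% and adds that "our goal is to reduce this incidence to about 10" per cent, "with a type I error of 0.05 and a power of 0.8". It continues: "Using a difference test for two-sample ratios, a sample size of 20 cases per group was calculated". No interim look appears there, and none appears among the tests named in the statistical analysis section.

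Randomization and Allocation concealment define one control arm (C0) and four probiotic arms (T1 to T4), "with 20 cases in each group". The stopping rule nevertheless speaks of the trial group in the singular. Harms mentions a committee that monitors safety and efficacy data, without a rule for it to apply.

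**The concern.** The efficacy rule ends the study, not one comparison. Read literally, any one of four probiotic arms could trigger it. Three things are then at stake.

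- **Error rate.** A second chance to declare significance raises the false-positive rate unless the interim level is strict or the final level is reduced. The protocol states one undivided 0.05.
- **Size of the reported effect.** The only expected difference in the document is 47% to 10%, or 37 points. A rule that requires the observed difference to reach it guarantees that no early stop can report less than that, whatever the truth.
- **The rest of the trial.** The other three probiotic arms would stop below 20 infants. So would the microbiota and metabolome outcomes, which the Abstract counts as primary and Endpoints as secondary.

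**Working it through.** **Inputs.** From the protocol: control rate 0.47, target rate 0.10, difference 0.37, alpha 0.05, power 0.80, 20 per arm, five arms. Assumed, because the protocol is silent: one interim look, its timing, ordinary two-sided 0.05 at both looks, and the test.

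**1. The stated sample size.** The unpooled formula, two-sided 0.05, with the unexplained 0.05 margin left out, gives

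n = (1.960 + 0.842)² × (0.47×0.53 + 0.10×0.90) / 0.37² = 7.849 × 0.3391 / 0.1369 = 19.44, so 20 per group.

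The stated figure is reproduced as a single-look calculation.

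**2. What can trigger a stop at 10 per arm (chi-square).** The statistic is z = difference / √[p̄(1−p̄)×2/10], and a stop needs z > 1.96.

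- 3/10 vs 0/10: 0.30/0.160 = 1.88, no stop
- 4/10 vs 0/10: 0.40/0.179 = 2.24, stop
- 5/10 vs 1/10: 0.40/0.205 = 1.95, no stop
- 6/10 vs 1/10: 0.50/0.213 = 2.34, stop

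The smallest difference that can stop the trial is 40 points.

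**3. Error rate, one probiotic arm vs control.** Exact binomial enumeration, both rates 0.47. The interim stop is for benefit only and needs both conditions; the final test is two-sided at 20 per arm.

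| Test | Look, per arm | No look | With look |
|---|---|---|---|
| Chi-square | 5 | 4.3% | 6.9% |
| Chi-square | 10 | 4.3% | 5.7% |
| Chi-square | 15 | 4.3% | 5.3% |
| Fisher's exact | 10 | 2.1% | 2.5% |

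With chi-square and a look at 10 per arm, false claims of benefit rise from 2.2% to 3.6%. In large samples with a look at half information (correlation √0.5), P(Z₁ > 1.96 or |Z₂| > 1.96) = 6.7%.

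**4. Four arms against one control.** Simulation (400,000 trials, unadjusted chi-square, look at 10 per arm) gives a familywise error of 13.3% without the look and 17.3% with it. The look adds 4.0 points; the rest is four-arm multiplicity.

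**5. Observed difference, given an early stop (chi-square, one arm).**

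| True difference | Look at 10: chance of stop | Look at 10: mean observed | Look at 15: mean observed |
|---|---|---|---|
| 0 | 2% | 53 points | 44 points |
| 20 | 13% | 54 points | 46 points |
| 37 | 42% | 54 points | 49 points |

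If any of the four arms can trigger the stop at 10 per arm, the chance of stopping is about 30% when every arm's true effect is 20 points, and 69% when it is 37.

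**6. Size at a stop.** Blocks of 5 over five arms put one infant per arm in each block. Ten per arm therefore means 50 infants, half of the planned 100.

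**7. Would a boundary fit 20 per group?** One look at half information, overall two-sided 0.05, same formula as step 1:

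| Boundary | Interim / final level | n per group |
|---|---|---|
| Haybittle-Peto | 0.001 / 0.0498 | 19.47, so 20 |
| O'Brien-Fleming | 0.0052 / 0.0480 | 19.68, so 20 |
| Pocock | 0.0294 / 0.0294 | 22.59, so 23 |

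**The case against.** The strongest objection is that this is a condensed article. Timing, boundary and alpha spending usually sit in an analysis plan or monitoring charter, and the rule itself refers to a planned analysis. That stands as far as the missing boundary goes. A reader might infer that the full 0.05 is kept for the final test after an interim test at nominal 0.05, but the protocol says neither. Its 0.05 may be the overall level, and step 7 shows that 20 per group fits a strict boundary just as well, so the sample size cannot settle it.

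The inflation is also modest and depends on the test. With Fisher's exact test, a natural choice at 10 to 20 per arm, the error stays well below 0.05. The textbook 8.3% for two looks at 0.05 does not apply, because it needs stopping in either direction and this rule stops only for benefit. The 17% familywise figure should not be blamed on the look, since about 13 points of it are there without one.

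A reader might further infer that day-30 data would be lost for infants already enrolled. Study procedure says that all subjects are followed for one month, so the loss is in numbers recruited.

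The objection does not reach the rule as written. Its trigger demands a 37-point observed difference, it names no comparison, and it ends the whole study. A boundary held elsewhere would not change the first or the third.

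**Conclusion.** The concern holds, at moderate severity. The protocol fixes an efficacy stop for the whole five-arm trial on an undefined significance criterion in an unspecified arm, and its sample size makes no mention of a look.

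The firmest part is the exaggeration. Taking the expected difference as 37 points, no stop can report less, and with chi-square looks at 10 or 15 per arm the mean reported difference is 44 to 54 points whether the truth is 0, 20 or 37. This applies only if the trial stops early.

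The error-rate part is conditional. With nominal 0.05 at both looks and chi-square, the per-comparison error is 5.3% to 6.9% depending on timing, against 4.3% without a look; Fisher's exact test shows no breach. The documents do not support a flat statement that the stated type I error is exceeded.

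**What to change.** Preferred: delete efficacy as a reason to stop the study and limit interim looks to safety, leaving the safety criterion untouched. This is one sentence in Interventions.

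If the efficacy stop is kept, state before any unblinded look:

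- that there is a single look, and when;
- which comparison can trigger it (the protocol ranks no arm, so this is the sponsor's choice);
- a strict boundary, for example Haybittle-Peto p < 0.001 with the final test at about 0.05;
- that one arm crossing it does not end enrolment in the others.

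Sample size should then mention the look. The number per group can stay at 20.

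The cost is that the option to stop early is largely lost. At 10 per arm with chi-square, p < 0.001 needs at least 8/10 vs 0/10, which occurs in about 1.5% of trials at 47% vs 10%. In a 100-infant trial that is a small price. Four-arm multiplicity at the final analysis is a separate matter that this change does not address.

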### Monitoring

The results obtained through this study may be published in medical journals, but all trial data and recorded information will be kept confidential in strict accordance with the law. The subjects' personal information will be kept strictly confidential and will not be disclosed unless required by the corresponding law or with their explicit consent. When necessary, the administrative department of the government and the hospital's ethical committee may consult the subjects' data in accordance with the regulations, but only after obtaining appropriate ethical and legal approvals.

This study will develop a data security monitoring plan based on the risk level. All adverse events will be documented in detail and properly handled and followed up until they are resolved or stabilized. Serious adverse events will be promptly reported to the ethics committees, competent authorities, initiators, and drug regulators.

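### Four of the five listed adverse events are defined only under probiotic use, so read literally they cannot be recorded in the phototherapy-only arm and have no equally ascertained comparator

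*Protocol article*

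**What the plan says.** All of the following is in the protocol article.

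- **Definition (Interventions, adverse event observation, item 1).** The first sentence reads: "adverse events are defined as severe vomiting, diarrhea, disruption of normal eating habits, or significant necrotizing enterocolitis occurring during the use of probiotics". The next sentence adds a fifth event with no such condition: "Additionally, an adverse event is defined as a severe increase in jaundice value that reaches the index for exchange transfusion".
- **Diagnostic criteria (item 2).** Severe vomiting means "vomit 5 or more times per day for 2 or more days". The diarrhea criterion is "Diarrhea 8 or more times per day for 2 or more days". Necrotizing enterocolitis (NEC) and exchange-level jaundice are diagnosed by guideline. Disrupted eating has no criterion.
- **Grades (item 3).** The lowest grade is "Mild: Neonates can tolerate the event, which does not affect treatment, does not require special treatment, and has no impact on the neonates' health". The highest is "Severe: The event endangers the neonate's life, potentially causing death or disability, and requires immediate emergency treatment".
- **Reporting (item 5).** Strict records, the adverse event form and the 24-hour notice apply when a neonate has an event after taking probiotics, or when the event is suspected to be related to them. The same item ends trial participation for a neonate with an adverse event.
- **General recording.** Item 6 puts all adverse events during treatment on the case report form and plans to analyse their potential relationship to probiotics. Study procedure says that any adverse events are documented at the start. Monitoring says: "All adverse events will be documented in detail and properly handled".
- **Control arm.** C0 receives phototherapy only (Abstract; Allocation concealment).

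**The concern.** An adverse event definition should not depend on the treatment under test. Here four of the five listed events carry a condition that C0 infants can never meet. Diarrhea is also among the side effects of phototherapy itself that the Introduction lists, so a background rate in C0 is to be expected. If staff follow the definition and the reporting trigger as worded, the same episode is an adverse event in T1 to T4 and nothing in C0.

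Two consequences follow. First, the relationship of adverse events to probiotics, which item 6 says will be analysed, would rest on probiotic arms with a background rate set against a control arm whose background was not recorded. Second, an adverse event ends an infant's participation under item 5, and one withdrawal criterion under Eligibility criteria is likewise worded around the probiotics intervention. On a literal reading, the same vomiting or diarrhea could remove an infant in T1 to T4 and leave one in C0. Both symptoms belong to the primary endpoint, so unequal removal could also reach the efficacy comparison.

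**Working it through.** **Step 1: which events can be recorded in C0, read literally**

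| Event in the definition | Needs probiotic use? | Possible in C0? | Also named in the primary endpoint? |
|---|---|---|---|
| Severe vomiting | yes | no | yes (vomiting) |
| Diarrhea | yes | no | yes |
| Disrupted eating | yes | no | in substance (feeding intolerance) |
| NEC | yes | no | no |
| Exchange-level jaundice | no | yes | no |

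The zero in C0 is therefore structural for four events, not for the whole adverse event count. NEC is the one event that is both tied to probiotic use and not named in the primary endpoint.

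**Step 2: fit between definition and grades**

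- Vomiting and diarrhea must pass daily count thresholds on 2 or more days, and NEC and exchange-level jaundice are serious by nature. Few of these can leave treatment and health unaffected, so the Mild grade fits poorly.
- The Moderate grade is usable. Vomiting or diarrhea at threshold that affects treatment without endangering life belongs there.
- Disrupted eating has no threshold and could take any grade.

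**Step 3: how large a spurious excess could be**

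The article gives no adverse event rate and no calculation on this point, so there is no stated figure to reproduce. The inputs are:

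- Arm sizes from Randomization: 5 arms of 20, so 4 × 20 = 80 probiotic infants and 20 in C0.
- Assumed: the true rate q of the four events combined is the same in every arm; C0 is recorded as 0/20; pooled probiotic arms are compared with C0 by a two-sided Fisher exact test at 0.05. The article plans no such test; it is used only to show scale.

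With 0/20 in C0, 14/80 gives p = 0.066 and 15/80 gives p = 0.037, so 15 or more events among the 80 are needed for p < 0.05. The chance of a false excess is then P(X ≥ 15) with X ~ Binomial(80, q). For comparison, the last column gives the chance that the test is significant in either direction when C0 events are counted in the same way.

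| Assumed q | Expected in T1–T4 (80q) | Expected in C0 if counted (20q) | Recorded in C0 | P(p < 0.05), C0 forced to 0 | P(p < 0.05), equal counting |
|---|---|---|---|---|---|
| 5% | 4 | 1 | 0 | 0.000 | 0.019 |
| 10% | 8 | 2 | 0 | 0.012 | 0.027 |
| 20% | 16 | 4 | 0 | 0.65 | 0.034 |
| 30% | 24 | 6 | 0 | 0.99 | 0.033 |

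For one probiotic arm (20) against a forced 0/20, the probabilities are 0.003, 0.043, 0.37 and 0.76 at the same four rates.

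False significance is thus a material risk only if the events are fairly common. The loss of the C0 background count (20q events) occurs at every rate.

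**The case against.** The case against runs as follows.

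- **The control arm is not at zero for all adverse events.** This stands. Exchange-level jaundice counts in every arm.
- **Harms can still be compared.** This stands in large part. Vomiting, diarrhea, feeding intolerance, rash, fever and convulsions are counted in the primary endpoint without a probiotic condition. Study procedure has side effects observed in subjects generally after phototherapy, and Table 1 schedules assessments with no arm restriction. A reader might infer that safety cannot be compared between arms at all; the article does not support that.
- **Other sentences speak of any or all adverse events, and some recording takes place before probiotics start.** This shows that the intent may be arm-neutral. But these sentences use the term that item 1 has just defined for this trial and do not redefine it. At best the text conflicts with itself.
- **The condition could mean the one-month intervention window.** That is possible, but the wording does not say so, and the reporting trigger in item 5 refers to actually taking probiotics.
- **Neonatologists are blinded, so they could not record by arm.** Blinding says this, but the Discussion says that the investigators would know the assignments. Blinding therefore cannot be relied on to repair the definition.
- **The 65% figure is selective.** It needs an assumed 20% rate of mostly high-threshold events, in a test that the article does not plan, while item 4 expects adverse events to be improbable. This stands, so the figure is only one point in a range.
- **The case report form is not shown.** This also stands. It may already record C0 events, so what happens in practice is unknown.

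**Conclusion.** The point holds in a limited form. As worded, the definition and the reporting trigger ascertain severe vomiting, diarrhea, disrupted eating and NEC unequally between C0 and T1 to T4. They also conflict with the article's own sentences on any or all adverse events. The analysis of the relationship to probiotics loses its comparator for these four events, and NEC is most exposed.

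The grading mismatch is confined mainly to the Mild grade. A reader might infer that only severe events qualify and that the Moderate grade is nearly empty too. That is not supported: disrupted eating has no threshold, and the count thresholds are a lower bar than the life-endangering Severe grade.

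The size is conditional. Under equal true rates and a forced 0/20, the chance of a falsely significant excess is about 0% at a 5% rate, 1% at 10% and 65% at 20%. These rates are assumptions. Since the article expects a low rate, the likelier harm is an uninterpretable adverse event table rather than a significant false signal. The wording should be corrected; no change in sample size follows.

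**What to change.** - In item 1 of the adverse event section, replace the condition on probiotic use by occurrence in any arm from randomization to day 30.
- Record events of any grade, and keep the listed thresholds as the definition of a special-interest subset. This also gives the Mild grade a purpose.
- Reword item 5 so that the same adverse event form is completed in C0 and T1 to T4. Relatedness to probiotics then becomes an item on the form, not the condition for opening it.
- Compare adverse events by randomized arm, with NEC reported for every arm.
- Reconcile the passages that end an infant's participation after an adverse event (withdrawal criteria under Eligibility criteria, and item 5) with the arm-neutral definition. Which clinical rule applies is for the investigators to decide.

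The cost is changes to protocol and case report form wording, and slightly more event recording at visits already scheduled for all arms.

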### Eligibility criteria

(1)Inclusion criteria: (1) Jaundice index: According to the American Academy of Pediatrics phototherapy guidelines, the jaundice index reaches the phototherapy threshold; (2) age ≤2 weeks; (3) Term infants with 37 weeks ≤ gestational age < 42 weeks and 2,500 g ≤ birth weight < 4,000 g; (4) No prior use of antibiotics or ecological agents before specimen collection; (5) Healthy mothers during pregnancy, with no history of special drug use, and no intake of antibiotics or microecological agents before, during, or after childbirth; (6) Enrolled infants were exclusively breastfed, exclusively formula-fed, or mixed-fed before admission; (7) All enrolled infants had neonatal pathological jaundice as defined by “Practical Neonatology” and required hospital admission solely for phototherapy; (8) Informed consent provided voluntarily.(2)Exclusion criteria: (1) Gestational age <37 weeks or ≥42 weeks; (2) bilirubin levels reaching the exchange blood transfusion standard or elevated direct bilirubin; (3) complications with pneumonia, septicemia, or other diseases; (4) patients with severe immunodeficiency diseases; (5) those with inherited metabolic diseases; (6) congenital biliary malformations or other organ malformations; (7) drug allergies; (8) situations that may warrant exclusion as determined by the researcher, such as a guardian with mental illness or frequent changes in living or working environments, which may result in loss of follow-up.(3)Elimination criteria: (1) Those refusing the use of their newborn information and their stools and blood; (2) During the treatment process, other drugs might be needed to be added because of other diseases, such as the use of antibiotics and micro-ecological agents.(4)Criteria for withdrawal from the study: (1) participants who suddenly refuse stool and blood collection and request to withdraw from the study; (2) severe gastrointestinal symptoms, such as intense vomiting, diarrhea, or abdominal distension, and other adverse events that significantly affect the treatment process during the probiotics intervention; (3) neonates requiring exchange blood transfusion due to the continued worsening of jaundice after active phototherapy; (4) neonates lost to follow-up, unreachable, or unable to return to the study center for visits.

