### Endpoints

(1)Primary endpoint: significant reduction in the incidence of clinical side effects (i.e., diarrhea, rash, fever, vomiting, convulsions, feeding intolerance, etc.).(2)Secondary endpoints: after the addition of probiotics, the intestinal flora will be maintained in a stable state after phototherapy, and the changes in metabolic indicators; changes in jaundice (i.e., serum bilirubin, bile acid and transcutaneous bilirubin data), feeding status, changes in urine volume and weight, and vital signs during phototherapy

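### Adverse events are defined by a closed list without infection, at odds with wider wording elsewhere, so infection in infants given live bacteria is not assured to be recorded as harm

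*Protocol article*

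**What the plan says.** Under Interventions, adverse event observation, item (1), "adverse events are defined as severe vomiting, diarrhea, disruption of normal eating habits, or significant necrotizing enterocolitis occurring during the use of probiotics". The same item adds one more event: "an adverse event is defined as a severe increase in jaundice value that reaches the index for exchange transfusion". Item (2) gives diagnostic criteria for vomiting, diarrhoea, necrotizing enterocolitis and exchange level only.

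Under Eligibility criteria, septicaemia bars entry through "complications with pneumonia, septicemia, or other diseases". Elimination criterion (2) covers infants for whom, during treatment, "other drugs might be needed to be added because of other diseases, such as the use of antibiotics and micro-ecological agents".

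Several places use the term more broadly:
- Withdrawal criterion (2) under Eligibility criteria provides for other adverse events besides severe gastrointestinal symptoms.
- The first stopping criterion under Interventions refers to serious adverse events possibly related to the probiotics.
- Adverse event observation, item (6): "Serious adverse events must be reported in strict accordance with the relevant provisions of GCP (Good Clinical Practice".
- Monitoring: "Serious adverse events will be promptly reported to the ethics committees, competent authorities, initiators, and drug regulators".

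The primary endpoint under Endpoints is a "significant reduction in the incidence of clinical side effects (i.e., diarrhea, rash, fever, vomiting, convulsions, feeding intolerance, etc".

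**The concern.** The product is live bacteria, and the infants are at most two weeks old at entry. Infection is an obvious harm to watch for, and the protocol recognises it at entry by excluding septicaemia and severe immunodeficiency. Once treatment has started, infection has no adverse-event category, while the drug that would treat it is a reason for elimination.

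The safety machinery runs on the defined term. The adverse event form and 24-hour notice (item (5)), the CRF grading and relationship analysis (item (6)) and the weekly review (Harms) all start from an adverse event. If site staff apply item (1) literally, an infection may start none of them, and a low or zero infection count at the end could not be relied on.

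**Working it through.** The check is mainly a comparison of text. No figure in the protocol bears on it except the group sizes.

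**Step 1: is the list closed?** Item (1) states a definition and contains no phrase such as 'for example' or 'any untoward event'. The endpoint list, by contrast, is left open at its end. The criteria in item (2) add no further event type. The list is closed, and it omits infection, fever and convulsions.

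**Step 2: what happens to an infant who develops an infection on treatment?**
- It matches none of the five listed events.
- If antibiotics are given, elimination criterion (2) is met.
- Table 1 marks the inclusion and exclusion criteria at every visit to day 30, so septicaemia could also be picked up there as an exclusion.
- The article does not say whether an adverse event form comes before elimination.

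**Step 3: does other wording widen the definition?**
- Withdrawal criterion (2) suggests that it does. Apart from gastrointestinal and feeding items, the list holds only exchange-level jaundice, and that has its own withdrawal criterion (3).
- The severe grade in item (3) reads "The event endangers the neonate's life, potentially causing death or disability, and requires immediate emergency treatment", which is not tied to the listed items.
- Serious-event reporting would cover life-threatening sepsis if serious adverse event takes its GCP meaning. The article does not say whether the closed list also limits that term.
- None of these clearly reaches a non-serious infection treated with antibiotics.

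**Step 4: are fever and convulsions lost?** No. Both are counted in the primary endpoint, body temperature is observed after phototherapy (Study procedure), and Table 1 has vital signs at every visit. They are missing only from the adverse-event route.

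**Step 5: how much could one missed case matter?** Randomization gives 20 infants in each of four probiotic groups: 4 × 20 = 80. The article states no infection rate, so the rates p below are assumptions. Expected cases are 80p, and the chance of at least one is 1 − (1 − p)^80.

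| Assumed p | Expected cases | Chance of at least one |
|---|---|---|
| 0.5% | 0.4 | 1 − 0.995^80 = 33% |
| 1% | 0.8 | 1 − 0.99^80 = 55% |
| 2% | 1.6 | 1 − 0.98^80 = 80% |
| 3% | 2.4 | 1 − 0.97^80 = 91% |

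The one-sided 95% upper limit after 0/80 is 1 − 0.05^(1/80) = 3.7%. After 1/80 it solves (1 − p)^80 + 80p(1 − p)^79 = 0.05. At p = 0.058 the left side is 0.008 + 0.041 = 0.050, so the limit is about 5.8%. One unrecorded case would thus move the observed rate from 1/80 = 1.25% to zero and the upper limit from about 5.8% to 3.7%.

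**The case against.** A reader might infer that sepsis would never be counted as harm and that the trial would report no infections whatever happened. The documents do not support that. It requires the list in item (1) to limit every other safety provision, and nowhere do they say so. The withdrawal criterion, the stopping criterion, the severe grade and the two serious-event reporting statements all point to a wider meaning. What stands is that the text is inconsistent, not that it guarantees a zero.

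A reader might also infer that eliminated infants drop out of safety reporting. The article is silent on this, and how they enter the safety tables is commonly left to the full protocol or analysis plan. That silence alone is no fault. It matters here only because a stated closed definition and a stated elimination rule meet in the same infant.

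Third, listing fever and convulsions as missed events would be wrong, since the primary endpoint counts them. Adding them to item (1) would also have a side effect: item (5) says the trial is terminated for a neonate with an adverse event, so infants reaching a primary-endpoint event could be taken out of the study.

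Finally, the infection rates above are assumptions for term infants admitted solely for phototherapy, and the article does not plan to report a limit based on 0/80. The arithmetic shows sensitivity to one case and nothing more.

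**Conclusion.** The point holds in a limited form. The adverse-event definition is closed and omits infection, it conflicts with the protocol's own wider use of the term, and antibiotic use leads to elimination. Recording of infection is therefore not assured, and the weakest place is a non-serious infection treated with antibiotics. For life-threatening sepsis the answer depends on whether serious adverse event is read in its GCP sense.

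The conclusion rests on the wording and needs no infection rate. Its practical size is small in cases but large in effect on the safety conclusion: at the assumed rates, 0.4 to 2.4 cases are expected among 80 infants. The wording should be corrected; the point does not affect the efficacy comparison.

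**What to change.** Reconcile the passages as follows.

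- In adverse event observation, items (1) and (2), make the definition open for recording: any untoward event, with infection and bacteraemia named.
- Require an adverse event form whenever an antibiotic is started, completed before elimination criterion (2) is applied.
- State that eliminated and withdrawn infants are counted in the safety tables of their randomised arm.
- State that the wider definition concerns recording and reporting only. Reconcile it with the sentence in item (5) on terminating the trial for a neonate with an adverse event, so that the wider definition does not by itself end participation.

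The cost is protocol and CRF wording, a few more adverse event forms, and the work of reconciling item (5). That last part cannot be skipped, because otherwise the wider definition would change who stays in the study.
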